## Statistical analysis

7

Statistical analysis was performed by SPSS26.0 software, and all test data were expressed as mean and standard deviation.

A total of two types of independent variables were used in this study, namely the group independent variable (FSN group and EA group) and the time independent variable (pre-intervention, after 1, 2, 3, and 4 weeks of intervention, and after follow-up), in which the time independent variable was a replicated independent variable. Data were tested for normality using the Shapiro–Wilk test and Leven’s test for chi-square. If the data conformed to normal distribution, two-way repeated measures ANOVA (Two-Way Repeated ANOVA) was used to observe the Main Effect and Interaction of the two types of independent variables, i.e., time independent variable (within-group) and subgroup independent variable (between-groups), on the dependent variable, and when there was an Interaction between the two, a Boneferroni’s *post hoc* test (*Post Hoc*) was used. η^2^ was used for the expression of the effect size: η^2^ < 0.06 is a small effect size. 0.06 ≤ η^2^ < 0.14 is a medium effect size. η^2^ ≥ 0.14 is a large effect size. If the distribution did not conform to normal distribution, the Scheirer-Ray-Hare test was used and results were expressed as median and interquartile spacing.

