The primary outcome is the response rate (32), which was defined as the proportion of participants who achieved minimal clinically important improvement (MCII) on both the NRS and the WOMAC functional scale. Minimal Clinically Important Improvement (MCII) is the smallest change in a patient’s symptoms that is important to improve, presenting the effect of the intervention at an individual level and can provide the patients and therapists to provide more direct information to decide whether to use the treatment or not. The MCII of the NRS is set at 2 points, and the MCII of the WOMAC functional subscale (Likert version 3.1) is set at 6 (33). Cun-Zhi Liu’s team used the response rate as the main evaluation index in an article published in the journal Arthritis & Rheumatology on the treatment of osteoarthritis of the knee with acupuncture (19). At present, many domestic and foreign scholars use response rate as the main observation index of KOA (32, 34). Secondary outcome indicators include the NRS, a modification of the VAS by Budzynski et al. The NRS is more responsive than the VAS and VRS (35). The WOMAC score was developed in 1988 by Bellamy et al. (36). It has a high degree of validity and reliability, which reflects treatment outcomes well and the WOMAC score is suitable for the assessment of chronic injuries (37). The 6MWT not only shows an individual’s level of endurance, but also assesses a patient’s walking ability (38). The patient is asked to walk for 6 minutes down a 30-meter corridor, and the distance he or she walks in the 6 minutes is measured (39). The 6MWT is currently recommended by the Osteoarthritis Research Society International (OARSI) (40) as one of a set of performance-based tests to assess a patient’s walking ability. In addition, pain and dysfunction will affect the quality of life of patients, and today’s society has higher and higher requirements for quality of life, so the assessment of the quality of life of patients before and after treatment is also crucial. In this study, we chose the SF-12 scale to assess the quality of life of patients, which is simpler and easier to use than the SF-36, and saves the time and cost and improves the rate of completion of the scale, which has been more widely used in the clinic (41). In this study, we will assess the patients’ situation from three aspects: pain, function and quality of life, which can respond to the patients’ problems more comprehensively.

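### The eta-squared bands in Section 7 have no negligible category, so a null FSN–EA result on a secondary score is labelled a small effect, and the label gives neither direction nor size in points

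*Protocol article*

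**What the plan says.** Section 7 (Statistical analysis) of the protocol article plans, for normally distributed scores, that "two-way repeated measures ANOVA (Two-Way Repeated ANOVA) was used to observe the Main Effect and Interaction" of group and time. Bonferroni post hoc tests follow if the two interact. For magnitude it states that "η^2^ was used for the expression of the effect size" and gives three bands:

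- lowest band: "η^2^ < 0.06 is a small effect size"
- middle band: called medium, from 0.06 up to but not including 0.14
- top band: called large, from 0.14 upward

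The bands cover every possible value, and none of them means negligible or no effect. The section also says that data are summarised by means and standard deviations. For non-normal data, "the Scheirer-Ray-Hare test was used and results were expressed as median and interquartile spacing"; no effect measure is named there.

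Two other places bear on the point. The Discussion states "The MCII of the NRS is set at 2 points"; for WOMAC function it gives a corresponding value of 6 points. The primary outcome (Section 6.1) uses cuts of 2 and 6 points to classify each patient as a responder by change from baseline. The sample-size section (3.5) sets a non-inferiority margin of −0.1 on the response rate.

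**The concern.** The stated aim is to compare the clinical efficacy of FSN and EA. A reader of the secondary results wants to know which arm did better, by how many points, and how precisely that is known. The effect size that the plan names cannot supply this:

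- **No floor.** Taken literally, an eta-squared of exactly 0 is a small effect.
- **No sign.** Eta-squared is a share of variance, so it is the same whether FSN or EA is ahead.
- **No unit.** It cannot be read in NRS points, WOMAC points or metres walked.
- **No stated term.** The ANOVA has a group effect, a time effect and an interaction, and the bands are not tied to any of them. A large value for time could reflect improvement common to both arms and say nothing about FSN against EA.

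At stake is the wording of the secondary results. A paper could report a small effect for scores on which the arms do not differ, or a large one that is not a treatment contrast.

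**Working it through.** **Inputs.** The bands come from Section 7. For the number of patients I use the range that follows from Section 3.5: 118 evaluable per arm, so 2 × 118 = 236, up to the full 300.

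**The plan's own figure.** With response rates 0.56 and 0.45, margin 0.10, one-sided alpha 0.025 and power 0.90:

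n = (0.56 × 0.44 + 0.45 × 0.55) × (1.960 + 1.282)² / (0.11 + 0.10)² = 117.7, which rounds up to 118 per arm.

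This agrees with the protocol. It does not involve eta-squared, so nothing below touches the sample size.

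**Label under a true null.** For a two-arm between-group term with normal errors and no true difference, eta-squared (group sum of squares over group plus between-patient error) follows a Beta(1/2, (N − 2)/2) distribution with mean 1/(N − 1). In the repeated-measures model the same holds for the group term, because that term is tested on each patient's average over visits.

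| N | Mean under null | P(below 0.06) | P(below 0.01) | Value at p = 0.05 |
|---|---|---|---|---|
| 236 | 1/235 = 0.0043 | 0.9999 | 0.874 | 0.0163 |
| 300 | 1/299 = 0.0033 | greater than 0.9999 | 0.916 | 0.0128 |

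Three things follow.

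1. Under a true null, the stated bands print *small* with probability above 0.999.
2. The *small* band runs across the significance boundary. At N = 300, a group term of 0.005 (not significant) and one of 0.05 (significant) carry the same label.
3. With a floor at 0.01 (a conventional value assumed here, not in the protocol), about 87% to 92% of null results would fall below *small*. A floor would therefore change what is printed, although 8% to 13% of nulls would still reach *small* or higher.

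**Width of the band.** For a simple comparison of two equal arms at one visit, eta-squared = d²/(d² + 4), so d = 2√(0.06/0.94) = 0.51 at the 0.06 cut. This equivalence is only indicative, because the planned model averages over visits.

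The effect of that averaging can be illustrated with assumed values: SD 12, correlation 0.5 between six visits, no baseline difference, and a constant 6-point difference at the other five visits.

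- Single visit: d = 6/12 = 0.50, so eta-squared = 0.25/4.25 = 0.059, labelled *small*.
- Group main effect over six visits: mean difference 5 × 6/6 = 5; SD of patient averages 12 × √((1 + 5 × 0.5)/6) = 9.17; d = 0.546; eta-squared = 0.298/4.298 = 0.069, labelled *medium*.

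The same treatment difference changes band with the term reported, which is why the term should be named. The group main effect also averages in the pre-intervention value, so it is not the week-4 difference.

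**The case against.** **The tests, not the bands, decide whether an effect exists.** This is correct. The main effects and interaction are tested in the same section, and nothing there treats the word *small* as evidence of a difference. A reader might infer that the plan would declare FSN and EA different under the null. The protocol does not support that; the defect is a misleading size label.

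**Direction and size can be recovered.** Arm means and SDs (or medians and interquartile ranges) will be reported, and post hoc comparisons are planned if there is an interaction. This stands in part: a reader can subtract the means, but no between-arm contrast is named as a result.

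**Eta-squared is not the whole plan.** True. The primary outcome is a response rate, with a margin of −0.1 on the difference between arms. The point is confined to the continuous secondary scores.

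**A condensed article may leave intervals to the full plan.** This also stands, so the absence of an interval is not itself the complaint. What remains is a rule that the article states and fixes badly.

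**The minimal clinically important improvements.** A reader might infer that the bands contradict the 2-point and 6-point values, since a 6-point WOMAC difference could be labelled *small*. The protocol does not support this. Those values classify individual patients by change from baseline; they are not thresholds for a difference between arm means. No SD is given either. Even if they were read as between-arm differences at a single visit, 2 NRS points would give 0.31 to 0.10 for assumed SDs of 1.5 to 3.0 (large to medium), and 6 WOMAC points 0.20 to 0.04 for SDs of 6 to 15 (large to small). No conflict follows from the document's own figures.

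**Conclusion.** The point holds as a minor one. The lowest band in Section 7 has no floor, so equal arms would be described as showing a small effect with probability above 0.999 at N = 236 to 300. That figure concerns the between-group term and assumes normal errors and no true difference; it needs no assumed SD. The label also lacks sign and unit and is not tied to a model term, so it does not convey the FSN–EA difference that the trial sets out to compare. The consequence is limited to the description of NRS, WOMAC, 6-minute walk and SF-12. The primary response rate, its margin, the sample size and the significance tests do not depend on the bands.

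**What to change.** In Section 7, make the FSN minus EA mean difference in scale points (metres for the walk test), with a 95% confidence interval, the reported effect measure for each continuous secondary outcome at week 4 and at the 4-week follow-up. Table 2 schedules all four measures at both times.

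If eta-squared is kept, state that it is descriptive, name the model term to which it refers, and add a negligible band, for example below 0.01.

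Do not adopt the 2-point and 6-point improvements as between-arm thresholds; they should remain individual responder criteria.

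The cost is one paragraph of analysis wording, with no new data, patients or software.

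### The fallback test for non-normal repeated scores (Scheirer-Ray-Hare) treats correlated visits as independent, so its group and group-by-time tests do not hold their nominal error rate

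*Protocol article*

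**What the plan says.** The Statistical analysis section of the protocol article defines two factors: treatment group and time. Time has six levels ("pre-intervention, after 1, 2, 3, and 4 weeks of intervention, and after follow-up"), which matches Table 2 (T0, T1 to T4, T8). The section recognises that time is measured within patients: "the time independent variable was a replicated independent variable".

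The choice of method then depends on a normality check: "Data were tested for normality using the Shapiro–Wilk test and Leven’s test for chi-square". If the check is passed: "If the data conformed to normal distribution, two-way repeated measures ANOVA (Two-Way Repeated ANOVA) was used". If it fails: "If the distribution did not conform to normal distribution, the Scheirer-Ray-Hare test was used". The section names no other method for non-normal data and describes no adaptation of the fallback to repeated measurements. It does not say whether the normality check is applied to raw scores or to residuals.

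The scores that follow this route are the repeated secondary outcomes in the Secondary outcomes section: NRS, WOMAC, 6-minute walk and SF-12. The primary outcome is a responder proportion at week 4.

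**The concern.** The two branches rest on different designs. Repeated measures ANOVA separates variation between patients from variation within patients. The Scheirer-Ray-Hare test ranks all observations together and refers each sum of squares, divided by the total mean square of the ranks, to a chi-square distribution. This is justified only if all observations are independent. A patient seen six times enters as six patients. Failing a check on distributional shape therefore also discards the within-patient structure that the same paragraph has just declared.

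The error goes in opposite directions for the two tests of interest. The group effect is judged against too small a variance, so a difference between FSN and EA is declared too easily. The group-by-time effect is judged against too large a variance, so a real difference in trajectory can be missed. Both bear on the secondary efficacy claims.

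**Working it through.** **Inputs from the article.** Two groups; six occasions (SF-12: three, at T0, T4 and T8 in Table 2); 118 evaluable and 150 randomised per arm.

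**The plan's own figure.** The Statistical analysis section gives no figure on this point. The 118 per arm in Sample size calculation sets the simulation size, and it reproduces: (1.96 + 1.2816)² × (0.56×0.44 + 0.45×0.55) / (0.56 − 0.45 + 0.10)² = 10.508 × 0.4939 / 0.0441 = 117.7, i.e. 118.

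**Assumptions not in the article.** Equal correlation ρ between any two visits of a patient, taken as 0.3, 0.5 and 0.7; NRS recorded in whole points from 0 to 10; SD 1.7 to 2.0 in the test simulations.

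**Step 1: group effect, closed form.** The variance of a patient's mean over T visits is 1 + (T − 1)ρ times what independence implies. The true error of a nominal 5% test is then 2 × [1 − Φ(1.96 / √(1 + (T − 1)ρ))].

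| ρ | √(1+5ρ) | Error, T = 6 | Error, T = 3 |
|---|---|---|---|
| 0.3 | 1.581 | 21.5% | 12% |
| 0.5 | 1.871 | 29.5% | 17% |
| 0.7 | 2.121 | 35.6% | 21% |

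Sample size does not appear in the formula, so recruiting more patients does not reduce the inflation.

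**Step 2: group-by-time effect, closed form.** Under the same correlation, the within-patient variance is (1 − ρ) times the total variance that the test uses as its yardstick. The true error is about P(χ² with 5 df > 11.07 / (1 − ρ)):
- ρ = 0.3: cut-off 15.8, error 0.7%
- ρ = 0.5: cut-off 22.1, error 0.05%
- ρ = 0.7: cut-off 36.9, error below 0.001%

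**Step 3: simulation.** Whole-point scores clipped to 0-10, six visits, 118 to 150 per arm, no group effect, with and without a common time trend.

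| ρ | Group effect | Group-by-time |
|---|---|---|
| 0.3 | 15-20% | at most 1.1% |
| 0.5 | 23-31% | at most 0.2% |
| 0.7 | 29-35% | 0.0% |

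With a time trend, the total mean square also contains the trend. This makes the fallback somewhat less liberal for group. At ρ = 0 without a trend, all effects were rejected in about 5% of runs (5.1-5.6%), so the fault lies in the ignored correlation.

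**Step 4: interaction power at 118 per arm.** For a difference growing to 0.6 points at week 4 and held at follow-up (SD 2), at ρ = 0.3 / 0.5 / 0.7:
- Repeated measures ANOVA: 0.43 / 0.58 / 0.81 (type I error 0.045-0.057)
- Scheirer-Ray-Hare: 0.10 / 0.05 / 0.01

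For larger differences (SD 1.7), Scheirer-Ray-Hare reached about 0.65-0.72 at 1.0 point and 0.99 or more at 1.5 points. The loss is heavy for small effects and negligible for large ones.

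**Step 5: how often the branch is entered.** Shapiro-Wilk at the 5% level (the article states no level), 118 or 150 scores, underlying normal variable:
- Whole-point NRS (means 2.5 to 6, SD 1.5 to 2.5): rejected in 100% of samples, and likewise for baseline scores cut off at the entry threshold of 4
- Half-point scores: 16-51%
- Quarter-point scores: 5-9%
- A 0-96 score, as an assumed WOMAC range: 4% to 100%, depending on floor and ceiling effects

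**The case against.** The defence concedes that the fallback ignores within-patient correlation. It contests how far the consequences reach, and most of that stands.

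- **Power.** A reader might infer from an interaction error near zero that the test has almost no power. That does not follow: a conservative test is not a powerless one. Power is nearly gone at 0.6 points, moderate at 1 point and essentially complete at 1.5 points. The article gives no expected difference in NRS, so the loss cannot be fixed at one value.
- **Trigger.** A reader might also infer that nearly all NRS data must enter this branch. That holds only for whole-point scores. The eligibility criteria use a mean NRS over two weeks, and Table 2 lists two NRS items (level walking and stairs) where the outcome sections speak of one pain score, so an averaged score is possible. Skewness or the entry cut-off could still cause rejection, but that has to be shown for the score actually analysed.
- **Scope.** For WOMAC, 6-minute walk and SF-12 the check may go either way, so it cannot be said that the secondary conclusions will be wrong; they could be, where the fallback is used. The primary outcome is binary and does not pass through this route.
- **Remedy.** Abolishing the normality switch goes beyond what this error demands.

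It is no defence that details may be left to a separate analysis plan. The article names a specific test, and that test does not fit the design it describes.

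**Conclusion.** The concern holds in limited form. The stated fallback is invalid for repeated measures. Where it is used with six visits, the group main effect has a type I error of about 15-35% instead of 5%, and the group-by-time test about 1% or less, with substantial power loss for small differences but not for large ones. With the three SF-12 assessments the closed form gives about 12-21% for the group effect.

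These figures rest on assumed within-patient correlations of 0.3-0.7, equal between all visits. Frequent use of the branch for NRS rests on the further assumption of whole-point scoring. Because the error is confined to a conditional branch for secondary outcomes and leaves the primary analysis and its sample size untouched, it should be corrected before analysis but does not undermine the trial.

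**What to change.** Replace the Scheirer-Ray-Hare test with a method valid for correlated data. Two suitable choices are a prespecified mixed model for repeated measures and a rank-based ANOVA for longitudinal data.

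A reasonable option, not required by this error, is to drop the normality switch and use one mixed model for all continuous scores, with the rank-based method as a sensitivity analysis. That would also make the choice of test independent of the scoring grid of the NRS.

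The cost is wording in the Statistical analysis section. Mixed models are available in the named software. Visits, data collection and sample size do not change.

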## Ethics and dissemination

8

The protocol was registered in the ClinicalTrials.gov Registry (No. ChiCTR2400080196) and was ethically approved by the Ethics Committee of Shandong Provincial Third Hospital, Shandong University (approval number: KYLL-2023092). The Institutional Ethics Committee of Shandong Provincial Third Hospital, Shandong University will be responsible for the safety and quality control of this study, and all researchers will comply with medical ethics during the trial. Before enrollment, patients will be fully informed about the clinical trial and sign an informed consent form. For CRF, confirmation of the completion of each patient’s name, randomization number, gender, intervention plan assignment, adverse events, and outcome indicators is required. All relevant patient information will be kept strictly secret. Data accessibility will require approval from an independent ethics committee 12 months after publication. Other researchers can request datasets by emailing the corresponding author. The results of this study will be published in peer-reviewed journals or as a paper.

## Discussion

9

Currently, the pathogenesis of KOA is not clear, and it is characterized by high morbidity and disability (2, 21). Relieving pain, slowing down the progression of the disease, improving the ability to walk, and improving the quality of life are the fundamental objectives of treating this disease (22).

EA is widely recognized internationally as an effective treatment for KOA. For example, the Chinese Orthopedic Association and the American College of Rheumatology (8, 23) have recommended the use of EA in the treatment of KOA, which can improve the clinical symptoms and quality of life of KOA patients (19). Many studies have shown that EA can regulate the expression of related cytokines, inhibit the apoptosis of chondrocytes, the degradation of cartilage extracellular matrix, and the generation of osteoclasts. In addition, EA can promote the proliferation of chondrocytes and cartilage repair, and play a bidirectional role in regulating the cartilage tissue, thus improving the patient’s knee joint lesions, and enhancing the clinical therapeutic effect (24). Moreover, In 2022 the UK NICE Association published a new version of its osteoarthritis guideline, which, based largely on the evidence from high-quality clinical studies by [name] team, concluded that electroacupuncture is clinically beneficial and cost-effective, and recommended the use of EA for the treatment of KOA (25). Evidently, EA therapy is mature and has been internationally recognized.

FSN is an emerging physical therapy in recent years, which is characterized by simple operation, fast effect, safety and green (26). It can sweep and pull the loose connective tissues to produce piezoelectricity and antipiezoelectricity effect, which breaks the energy crisis of the local affected muscles, and then cooperate with the reperfusion activities to relax the muscles and accelerate the blood circulation, so as to achieve the purpose of relieving the pain (27). In addition, the needling site of FSN is not at acupoints but at the normal tissues surrounding the myofascial excitation pain point (MTrP), which acts at the subcutaneous level of loose connective tissue (12, 28). It has been shown that (29) stretching has a direct mechanical effect on the inflammation-regulating molecules in connective tissues, and that when mechanical strain is produced by external forces, the crystals become electrodepolarized or electrically fielded, generating a positive piezoelectric effect; the channels of loose connective tissues are composed of proteins and mucopolysaccharides with semiconducting properties, and themselves contain a large amount of body fluids, and therefore transmit information up to three times faster than in the nervous system (30, 31). However, there is a lack of large sample clinical studies on the improvement of KOA by FSN. The results of this study will investigate whether FSN can be a viable and effective treatment.

The mandatory point of needle insertion in this study was selected with reference to the article published by Zhonghua Fu’s team (11, 15), which was the upper 1/3 of the line connecting the anterior superior iliac spine and the lateral superior edge of the patella. The optional points for needle insertion were selected based on clinical experience, according to the subjects’ different pain sites, clinical manifestations, and the location of the affected muscles, and 1–3 optional points were selected for the gastrocnemius muscle, tibialis anterior muscle, rectus femoris muscle, suture muscle, and soleus muscle.

The primary outcome is the response rate (32), which was defined as the proportion of participants who achieved minimal clinically important improvement (MCII) on both the NRS and the WOMAC functional scale. Minimal Clinically Important Improvement (MCII) is the smallest change in a patient’s symptoms that is important to improve, presenting the effect of the intervention at an individual level and can provide the patients and therapists to provide more direct information to decide whether to use the treatment or not. The MCII of the NRS is set at 2 points, and the MCII of the WOMAC functional subscale (Likert version 3.1) is set at 6 (33). Cun-Zhi Liu’s team used the response rate as the main evaluation index in an article published in the journal Arthritis & Rheumatology on the treatment of osteoarthritis of the knee with acupuncture (19). At present, many domestic and foreign scholars use response rate as the main observation index of KOA (32, 34). Secondary outcome indicators include the NRS, a modification of the VAS by Budzynski et al. The NRS is more responsive than the VAS and VRS (35). The WOMAC score was developed in 1988 by Bellamy et al. (36). It has a high degree of validity and reliability, which reflects treatment outcomes well and the WOMAC score is suitable for the assessment of chronic injuries (37). The 6MWT not only shows an individual’s level of endurance, but also assesses a patient’s walking ability (38). The patient is asked to walk for 6 minutes down a 30-meter corridor, and the distance he or she walks in the 6 minutes is measured (39). The 6MWT is currently recommended by the Osteoarthritis Research Society International (OARSI) (40) as one of a set of performance-based tests to assess a patient’s walking ability. In addition, pain and dysfunction will affect the quality of life of patients, and today’s society has higher and higher requirements for quality of life, so the assessment of the quality of life of patients before and after treatment is also crucial. In this study, we chose the SF-12 scale to assess the quality of life of patients, which is simpler and easier to use than the SF-36, and saves the time and cost and improves the rate of completion of the scale, which has been more widely used in the clinic (41). In this study, we will assess the patients’ situation from three aspects: pain, function and quality of life, which can respond to the patients’ problems more comprehensively.

There are some limitations to this study. Firstly, it was not possible to blind both the operator and the participants. Therefore, the applicability of the results to other populations needs to be carefully considered. Secondly, patients recruited from various centers may differ in gender, age, and other disorders. Therefore, subgroup analyses may be needed to determine the effectiveness of FSN for different subgroups. Thirdly, this study did not have a sham-Fu’s subcutaneous-needle group and therefore could not remove the placebo effect. Considering these limitations, we will carefully interpret our results.
